
**Fig. 1 Fig1:**
[figure not shown]
Outline of the Guideline for Exercise in Multiple Sclerosis (GEMS) program

**Table 2 Tab2:** Summary of Guidelines for Exercise in Multiple Sclerosis program features

**Feature**	**Description**
Prescription	Guidelines for Exercise in MS
	Progressive
	Individualized
Frequency	3 times per week
Exercise Session Duration	Approximately 1 h
Exercise Session Intensity	Moderate
	100 steps/min (pedometer)
	Rate of Perceived Exertion (RPE) between 11–13
Intervention Length	16 weeks
Meeting with Coach	
Weeks 1–4	Weekly
Weeks 5–8	Bi-weekly
Weeks 9–16	Monthly
Setting	Home
Supervision	
Who	Trained personnel
Mode	Remote, telecoaching
Exercise Modes	
Aerobic	Walking
Resistance	Bands, body weight
Materials Provided	Program Manual
	Newsletters
	Logbook
	Calendar
	Online Exercise Videos Accessible through QR Code
Equipment Provided	Pedometer
	Bands
Training Oversight	Zoom/Exercise Videos
Behavioral Intervention	Zoom
Intervention Safety	Fall Risk Assessment
	NMSS Resources
	Fall Prevention Instructions
	Zoom Oversight and AE/SAE Reporting

The table and its contents are adapted from our previous research using the same intervention [18–22]

**Table 3 Tab3:** Progression of the 3 levels of individualization of the Guidelines for Exercise in Multiple Sclerosis program

Week	Orange		Blue		Green	
	Aerobic training	Resistance training	Aerobic training	Resistance training	Aerobic training	Resistance training
	Phase I					
1	10 min, ~ 1000 steps			1S, 10R, 5E		
2	10 min, ~ 1000 steps			1S, 12R, 5E		
	Phase II					
3	15 min, ~ 1500 steps	1S, 15R, 5E	15 min, ~ 1500 steps	1S, 12R, 5E	10 min, ~ 1000 steps	1S, 12R, 5E
4	20 min, ~ 2000 steps	2S, 10R, 5E	15 min, ~ 1500 steps	1S, 15R, 5E	15 min, ~ 1500 steps	1S, 12R, 5E
5	25 min, ~ 2500 steps	2S, 12R, 5E	20 min, ~ 2000 steps	2S, 10R, 5E	15 min, ~ 1500 steps	1S, 15R, 5E
6	30 min, ~ 3000 steps	2S, 15R, 5E	20 min, ~ 2000 steps	2S, 12R, 5E	20 min, ~ 2000 steps	2S, 10R, 5E
7	30 min, ~ 3000 steps	2S, 15R, 6E	25 min, ~ 2500 steps	2S, 15R, 5E	20 min, ~ 2000 steps	2S, 10R, 5E
8	30 min, ~ 3000 steps	2S, 15R, 6E	30 min, ~ 3000 steps	2S, 15R, 5E	25 min, ~ 2500 steps	2S, 12R, 5E
9	30 min, ~ 3000 steps	2S, 15R, 7E	30 min, ~ 3000 steps	2S, 15R, 6E	25 min, ~ 2500 steps	2S, 12R, 5E
10	30 min, ~ 3000 steps	2S, 15R, 7E	30 min, ~ 3000 steps	2S, 15R, 6E	30 min, ~ 3000 steps	2S, 15R, 5E
11	30 min, ~ 3000 steps	2S, 15R, 8E	30 min, ~ 3000 steps	2S, 15R, 7E	30 min, ~ 3000 steps	2S, 15R, 6E
12	30 min, ~ 3000 steps	2S, 15R, 8E	30 min, ~ 3000 steps	2S, 15R, 8E	30 min, ~ 3000 steps	2S, 15R, 6E
13	30 min, ~ 3000 steps	2S, 15R, 9E	30 min, ~ 3000 steps	2S, 15R, 8E	30 min, ~ 3000 steps	2S, 15R, 7E
14	30 min, ~ 3000 steps	2S, 15R, 9E	30 min, ~ 3000 steps	2S, 15R, 9E	30 min, ~ 3000 steps	2S, 15R, 8E
15	30 min, ~ 3000 steps	2S, 15R, 10E	30 min, ~ 3000 steps	2S, 15R, 10E	30 min, ~ 3000 steps	2S, 15R, 9E
16	30 min, ~ 3000 steps	2S, 15R, 10E	30 min, ~ 3000 steps	2S, 15R, 10E	30 min, ~ 3000 steps	2S, 15R, 10E

*S* number of sets, *R* number of repetitions, *E* number of exercises

The table and its contents are adapted from our previous research using the same intervention [18–22]

**Table 4 Tab4:** Behavioral coaching session content

Week 1 Introduction to program	*Tele/Video-chat 1:* Clarification of materials received and initial questions; Explanation of program; Planning exercise schedule; Using the log-book; *Newsletter 1;* Exercise expectations; Exercise outcomes; Importance of this knowledge
Week 2 Outcome expectations	*Tele/Video-chat 2:* Compliance with program; Using the manual and log-book; Identifying personal outcomes
Week 3 Choosing a program	*Tele/Video-chat 3;* Compliance with program; Comparison of orange, blue and green programs; Choosing a program; *Newsletter 2;* Self-monitoring defined; Benefits of self-monitoring; Importance of this knowledge
Week 4 Self-monitoring	*Tele/Video-chat 4:* Compliance with program; Using your pedometer; Understanding exercise intensity
Week 5 Goal-setting	*Tele/Video-chat 5:* Compliance with program; Setting SMAART goals; Performing resistance training exercises correctly; Tracking progress; *Newsletter3;* Specific, measurable, adjustable, action-oriented, realistic, and time-limited exercise related goals defined; Importance of this knowledge
Week 7 Self-efficacy	*Tele/Video-chat 6:* Finding your self-confidence; What to do when you feel like quitting; Involving family; *Newsletter 4;* Self-efficacy defined; Experiencing success, choosing role models, accepting encouragement & managing physical and emotional responses; Reminder that program is specific for persons with MS
Week 11 Overcoming Barriers	*Tele/Video-chat 7:* Identifying your barriers; Making plans to overcome obstacles; Dealing with MS symptoms; *Newsletter 5;* Exercise barriers defined; Common barriers (facilities, social & symptoms); Strategies to overcome barriers
Week 15 Identifying facilitators	*Tele/Video-chat 8:* How to keep going on your own; Making adjustments as needed; Setting future goals; *Newsletter 6;* Exercise facilitators defined; Common facilitators (having a goal, enjoyment, social support, knowledge); Using facilitators long term

The table and its contents are adapted from our previous research using the same intervention [18–22]

### Control condition – home-based stretching and flexibility program

This program has been described in our previous research [22] and was developed based on a RCT of exercise training for improving mobility in MS [51] and two RCTs of exercise training for cognitive dysfunction in MS [61, 62]. The program itself has identical components as the GEMS program for aerobic and resistance exercise training, but focuses on stretching for improving flexibility and range of motion as important components of fitness. The program itself is based on *Stretching for People with MS: An Illustrated Manuel* from the National MS Society (Table 5), as this is MS specific and enhances the credibility of the control condition. Participants will be provided with a yoga pad (i.e., exercise equipment) and a manual, log-book, calendar, and prescription for the stretching program. This program includes newsletters focusing on SCT for behavior change, and video-chats with behavioral coaches that provide motivation and social accountability. The video-chats occur on the same timeline and frequency as the GEMS exercise training program in the intervention condition, but focus on the SCT constructs applied for stretching. We further monitor safety and compliance as done in the intervention condition, and provide resources and instruction on safety. Importantly, this condition accounts for the possible influences of social-contact and attention associated with the GEMS program on the study outcomes, and this represents a major advancement over waitlist control and standard of care conditions in previous RCTs of exercise training and depression in MS [10, 15–17].

**Table 5 Tab5:** Progression of the 3 levels of individualization of the stretching prescription

Week	Orange	Blue		Green
	Phase I			
1	10 min, 5 categories		2S, 2E, 15 s	
2	10 min, 5 categories		2S, 2E, 15 s	
	Phase II			
3	15 min, 5 categories 2S, 3E, 25 s	15 min, 5 categories 2S, 3E, 20 s		10 min, 5 categories 2S, 2E, 15 s
4	20 min, 5 categories 3S, 3E, 30 s	15 min, 5 categories 2S, 3E, 20 s		15 min, 5 categories 2S, 3E, 20 s
5	25 min, 5 categories 3S, 4E, 45 s	20 min, 5 categories 2S, 3E, 30 s		15 min, 5 categories 2S, 3E, 20 s
6	30 min, 5 categories 4S, 4E, 60 s	20 min, 5 categories 3S, 3E, 30 s		20 min, 5 categories 3S, 3E, 30 s
7	30 min, 6 categories 4S, 4E, 60 s	25 min, 6 categories 3S, 3E, 45 s		20 min, 6 categories 3S, 3E, 30 s
8	30 min, 6 categories 4S, 4E, 60 s	30 min, 6 categories 4S, 4E, 60 s		25 min, 6 categories 4S, 3E, 45 s
9	30 min, 7 categories 4S, 4E, 60 s	30 min, 7 categories 4S, 4E, 60 s		25 min, 7 categories 4S, 3E, 45 s
10	30 min, 7 categories 4S, 4E, 60 s	30 min, 7 categories 4S, 4E, 60 s		30 min, 7 categories 4S, 4E, 60 s
11	30 min, 8 categories 4S, 4E, 60 s	30 min, 8 categories 4S, 4E, 60 s		30 min, 8 categories 4S, 4E, 60 s
12	30 min, 8 categories 4S, 4E, 60 s	30 min, 8 categories 4S, 4E, 60 s		30 min, 8 categories 4S, 4E, 60 s
13	30 min, 8 categories 4S, 4E, 60 s	30 min, 8 categories 4S, 4E, 60 s		30 min, 8 categories 4S, 4E, 60 s
14	30 min, 8 categories 4S, 4E, 60 s	30 min, 8 categories 4S, 4E, 60 s		30 min, 8 categories 4S, 4E, 60 s
15	30 min, 8 categories 4S, 4E, 60 s	30 min, 8 categories 4S, 4E, 60 s		30 min, 8 categories 4S, 4E, 60 s
16	30 min, 8 categories 4S, 4E, 60 s	30 min, 8 categories 4S, 4E, 60 s		30 min, 8 categories 4S, 4E, 60 s

*S* number of sets, *E* number of exercises

The table and its contents are adapted from our previous research using the same control condition [22]

### Procedure

The study procedure is administered by a project coordinator with oversight by the PI and Co-Is, and monitored through a fidelity monitoring plan (Table 6). As done in our previous research [18–22], the project coordinator will contact interested participants via telephone, describe the study and its requirements, and then conduct the screening for inclusion/exclusion criteria. The project coordinator will then distribute the informed consent document electronically among participants who meet inclusion criteria further information about the study. This will be followed by a telephone call that ensures participants received the document and understand the study and research procedures. The project coordinator will further work with participants in obtaining physician approval for participation and verification of MS diagnosis as a final step in enrollment.

**Table 6 Tab6:** Overview of fidelity monitoring plan

		Areas of fidelity monitored				
Data source	Monitoring frequency	Study design	Provider training	Treatment delivery	Treatment receipt	Treatment enactment
Coaching call checklist	Monthly	** × **	** × **	** × **		
Coaching call logs	Monthly	** × **		** × **		
Auditing of coaching calls by expert	Weekly	** × **	** × **	** × **	** × **	
Behavioral resource bank within treatment group	Quarterly	** × **				
Review of participant exercise logbook	Weekly/ Monthly				** × **	** × **
Team meetings to discuss participant progress and protocol adherence	Weekly	** × **	** × **	** × **	** × **	** × **

The project coordinator will schedule baseline data collection, and provide written and verbal instructions regarding the baseline testing procedures. The project coordinator will send the participant document with directions and parking information, and contact the participant electronically and through telephone 24-h before the appointment as a reminder. Upon arrival, the project coordinator will review the study procedures with the participant, obtain written informed consent, and then initiate the baseline data collection.

The baseline data collection will be undertaken by treatment-blinded researchers who will start with a PAR-Q for ensuring safety and then administer measures of depression severity (i.e., primary outcomes) followed by the BICAMS and measures of fatigue and HRQOL (i.e., secondary outcomes). The participant will then undertake the maximal exercise test and muscle strength testing with a 15-min break between the measures of fitness. The competition of those measures will take ~ 120 min based on our previous experiences.

The treatment-blinded researchers will provide the participant with a packet containing an accelerometer along with GLTEQ. This packet will include instructions regarding the importance of wearing the accelerometer as instructed every day during the seven-day period, and provide a pre-stamped and pre-addressed envelope for return postal service. The participants will wear the accelerometer for a seven-day period and then complete the GLTEQ. The project coordinator will send brief, scripted e-mails for reminding participants about wearing the accelerometer in the middle of the seven-day period. This will be followed by a telephone call verifying that participants wore the accelerometer daily during the seven-day period and returned it along with the GLTEQ through the United States Postal Service.

Of note, demographic and disease-related characteristics will be collected from participant interviews and verification forms from the treating Neurologist, respectively. The patients will further provide a list of current medications and ongoing treatments for MDD and other symptoms of MS.

Once the baseline assessment is completed, participants will be randomly assigned into either the intervention or control conditions using a random numbers sequence with concealed allocation. The project coordinator will receive information on allocation, record it in a database, and communicate the condition of assignment with the participant and behavioral coaches. Importantly, several strategies will be adopted for maintaining blinded conditions. The behavioral coaches and other study staff are located in a separate lab space from where the treatment-blinded researchers administer outcomes. The behavioral coaches will emphsize among participants the importance of not revealing what type of exercise is being undertaken when interactiong with outcome assessors. The study staff will remind participants about not revealing the type of exercise being undertaken before the outset of follow-up outcome assessments.

The intervention/control conditions will be delivered by behavioral coaches who are univolved in outcome assessments in 12, partially overlapping waves of ~ 12 participants per wave, and the conditions will be delivered across a 4-month period. This use of waves will afford additional time for behavioral coaching during the one-on-one chat sessions than if enrolling 146 in one recruitment wave. This should permit greater penetration of the study materials. Participants will be asked to contact the project coordinator via the dedicated toll-free telephone number or e-mail in the occurrence of an adverse event or any other problem; this information will further be collected during video chats with behavioral coaches. The project coordinator will administer the PHQ-9 on the same weeks as the behavioral chats for ongoing monitoring of the mood status of participants.

The participants will complete the same measurement procedures immediately (i.e., immediate follow-up; 4 months) and 4-months (i.e., long-term follow-up; 8 months) after initiating the intervention/control conditions. There will be no behavioral coaching session during the long-term follow-up period for examining sustainability.

Participants will receive $100 USD remuneration for completing the measures per assessment period, including baseline, for a total of $300 USD. We will collect formative feedback using a Qualtrics survey for identifying opportunities for intervention improvement and refinement; this will be undertaken by participants after completion of the study.

### Data analyses

#### Overview

The data analyses will be overseen by a biostatistician and follow intent-to-treat (ITT) principles (i.e., include all persons regardless of dropout). We will perform exploratory data analyses only among those who complete immediate and long-term follow-up testing (i.e., completer’s or per protocol analysis). We will check the data for errors and outliers, and lock the data set before analyses. The analytic plan will account for potential confounders of the intervention effect on the outcomes. The confounders may include MS duration, BMI, age, sex, disease-modifying therapy, and relapse rate. We will include any of those variables and others that differ between conditions as covariates in the following analyses.

#### Data analysis – aim 1

The first analysis tests the hypothesis that those who are randomly assigned into the intervention condition (i.e., exercise training) will demonstrate (a) reductions from baseline in depression severity that (b) are sustained over 4-months of follow-up compared with those in the control condition (i.e., stretching). The hypothesis will be tested using a linear mixed model in JMP Pro 16.0. The linear mixed model will include condition and time as fixed effects, and subject nested within condition as a random effect using unbounded variance components and the REML method (https://www.jmp.com/content/dam/jmp/documents/en/academic/learning-library/08-repeated-measures-analysis-(mixed-model).pdf). The hypothesized interaction term will be decomposed with follow-up tests, and differences in comparison of mean scores will be expressed as Cohen’s d with standard guidelines for interpretation. The final models for PHQ-9 and HDRS-17 scores will be adjusted for covariates. The overall Type I error will be controlled based on an adjustment of alpha (two-tailed *α* = 0.025) given the two primary outcomes in Aim 1.

#### Data analysis – aim 2

The second set of analyses test the hypotheses that those who are randomly assigned into the intervention condition (i.e., exercise training) will report (a) improvements from baseline in fatigue, cognitive performance, and QOL that (b) are sustained over 4-months of follow-up compared with those in the control condition (i.e., stretching). Those hypotheses will be tested with the same modeling approach described for Aim 1. The overall Type I error will be controlled using a step-down procedure testing first fatigue, followed by domains of cognitive performance (SDMT, CVLT-II, and then BVMT-R), and lastly HRQOL [63].

#### Data analysis – aim 3

The third set of analyses test the hypotheses that those who are randomly assigned into the intervention condition (i.e., exercise training) will report (a) improvements from baseline in exercise behavior, free-living PA, and aerobic capacity and muscle strength that (b) are sustained over 4-months of follow-up compared with those in the control condition (i.e., stretching). Those hypotheses will be tested with the same modeling approach described for Aim 1. The overall Type I error will be controlled using a step-down procedure testing first exercise behavior and free-living PA, followed by aerobic capacity and muscle strength as outcomes [63].

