#### Power analysis and sample size

The power analysis was conducted in G*Power, Version 3.1 using F test for Test family and ANOVA: Repeated measures, within-between interaction for Statistical test. We estimated the sample necessary for detecting a Condition (2 levels of between-subjects factor: Intervention vs. Control) × Time (2 levels of within-subjects factor: 0 and 4 months) interaction on the primary outcomes of depression severity (i.e., 9-item Patient Health Questionnaire (PHQ-9; [36]) and Hamilton Depression Rating Scale (HDRS-17; [37]). We did not include 3 time-points as this assumes linear change across all 3 time points in G*Power 3.1, and we expected change between 0 and 4 months for the intervention condition, followed by stability between 4 and 8 months. The effect size (Cohen’s *f* = 0.18) was from our previous meta-analyses [15] regarding the effect of exercise training on depressive symptoms in persons with MS. The power analysis included assumptions of reliability for the within-subjects factor of ICC = 0.50, two-tailed *α* = 0.025, and *β* = 0.05 (i.e., 95% power); the *α* = 0.025 was selected based on two primary outcomes. The power analysis indicated the minimal total sample size for testing the Time × Condition interaction of 122 participants (61 per group), and we anticipate a dropout rate of ~ 20% resulting in a projected recruitment of 146 participants.

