### Random assignment

After collection of baseline data, participants will be randomly assigned into either the exercise training condition or the control condition using a computerized process based on a random numbers sequence, and group allocation will be concealed. Participants will not be informed directly that the exercise training condition represents the experimental treatment condition and the stretching condition (i.e., attention and social contact control condition) represents the control condition, as both conditions are based on guidelines and likely have benefits in MS. To do this, the study will be advertised as comparing two different exercise approaches for managing consequences of MS and improving health indicators among persons with MS. We will measure treatment credibility after the first assigned treatment session using an adaptation of the Reaction to Treatment Questionnaire (RTQ) [58].

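### Covariates for the final primary models are chosen by observed differences between arms, from an open list with no cut, so the models are not fixed until allocation is seen

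*Protocol article*

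**What the plan says.** The rule is in the protocol article, Data analyses, Overview. Candidates come first: "The confounders may include MS duration, BMI, age, sex, disease-modifying therapy, and relapse rate". The entry criterion follows: "We will include any of those variables and others that differ between conditions as covariates in the following analyses". No test, threshold or effect size defines a difference, and the further variables are not limited.

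The section Data analysis – aim 1 applies this to both primary outcomes: "The final models for PHQ-9 and HDRS-17 scores will be adjusted for covariates". The model itself is stated as "The linear mixed model will include condition and time as fixed effects, and subject nested within condition as a random effect", with the interaction of the two as the hypothesised term. Whether covariates enter as main effects or are crossed with time is not stated. No unadjusted or fixed-covariate model is named as primary. Aims 2 and 3 use the same approach and so inherit the rule.

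The one timing safeguard is "We will check the data for errors and outliers, and lock the data set before analyses". The Random assignment section describes allocation "using a computerized process based on a random numbers sequence, and group allocation will be concealed". The Procedure section says participants supply at baseline a "list of current medications and ongoing treatments for MDD and other symptoms of MS".

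**The concern.** When allocation is random and concealed, a baseline difference between arms is a chance event. It says nothing about whether the variable predicts depression severity. A rule that admits variables because they differ can bring in ones with no bearing on the outcome and leave out useful ones that happen to be balanced. Treatment for MDD, recorded at baseline, is not on the named list and would enter only if the arms differed on it.

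The second problem is that the final model cannot be written down in advance. Three elements are open: which variables are candidates, what counts as differing, and how covariates enter. Locking the data does not close them, because a difference between arms can be judged only with allocation known. At stake is whether the primary analysis is fixed before the result can be seen.

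**Working it through.** **1. The plan's own figure.** Inputs from Power analysis and sample size: f = 0.18, two-tailed alpha 0.025, power 95%, correlation 0.50, two time points. The noncentrality is λ = f²·N·m/(1−ρ), with df 1 and N−2. At N = 122, λ = 0.0324 × 122 × 2 / 0.50 = 15.81 and power is 0.955. The smallest N reaching 95% is 120 (power 0.952), so 122 is reproduced within tolerance. No covariate enters this calculation. With these inputs f corresponds to a difference in change of 4f = 0.72 SD.

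**2. How often some covariate differs by chance.** For k independent candidates and cut c, the probability is 1 − (1−c)^k. The document gives k = 6; the cuts are assumptions, since none is stated.

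| Cut | Six candidates | Twelve candidates (assumed, because the list is open) |
|---|---|---|
| p<0.05 | 1 − 0.95⁶ = 26% | 46% |
| p<0.10 | 1 − 0.90⁶ = 47% | 72% |
| p<0.20 | 1 − 0.80⁶ = 74% | 93% |

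Correlation among the candidates (age and MS duration, say) would lower these figures. The spread across cuts shows how much depends on an unstated threshold.

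**3. Type I error.** Simulation with 61 per arm, correlation 0.5, alpha 0.025, six independent covariates, selection at p<0.05 and 20,000 runs per null scenario. The document gives no prognostic strength, so the covariates' R² for follow-up beyond baseline was assumed at 0.10, 0.20 and 0.30. Applied mechanically, the selection rule rejected in 0.020 to 0.023 of runs. Reporting the most favourable of the unadjusted, selected and fully adjusted models gave 0.035 to 0.039. That last figure is for a baseline-adjusted comparison at 4 months.

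**4. Does adjustment touch the planned test?** A mixed model of the stated form was fitted to one simulated data set (122 participants, three visits). With complete data, the condition-by-time estimates were −0.505 and −0.415 (SE 0.171), and identical after adding a baseline covariate as a main effect. With 20% dropout the 4-month estimate moved from −0.473 to −0.513, with SE 0.191 in both fits.

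**5. Where prognostic covariates would help.** Power, imbalance-selected against pre-specified adjustment, at a 0.5 SD difference (4,000 runs each):

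| Assumed R² | 4-month comparison, baseline-adjusted | Change score, covariates acting on change |
|---|---|---|
| 0.10 | 83.1% vs 84.8% | 70.7% vs 71.7% |
| 0.20 | 81.2% vs 87.5% | 67.8% vs 73.6% |
| 0.30 | 82.9% vs 93.1% | 70.1% vs 78.8% |

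The gap is about 1 to 10 points. At the planned 0.72 SD it is about 0.5 to 2 points. In the change-score comparison at 0.5 SD, no adjustment gave 70.9%, 67.9% and 69.6%, essentially the same as the selection rule. The gap is therefore a gain forgone, not power lost from the plan.

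**The case against.** Four objections deserve an answer.

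*Power.* A reader might infer that the rule costs the trial power. The document does not support that for its primary test. The interaction is unchanged by main-effect covariates when data are complete, its standard error hardly changes under 20% dropout, and the sample size never counted on adjustment. This objection stands. A power argument applies only to between-arm comparisons at follow-up or to covariates crossed with time.

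*Type I error.* A reader might also infer that the rule inflates false positives. At one fixed cut it does not; it is slightly conservative. Inflation needs an analyst to compare models and report the best, and the article describes no such step. That also stands. What remains is that the wording would not prevent it.

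*Baseline severity.* It would be wrong to say that the model ignores the main predictor of outcome. The month-0 score is already in the model as a response.

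*Wording and the analysis plan.* The sentence can be read as always including the six variables and selecting only the others, and an analysis plan not shown may set the cut and the list. On that reading the percentages apply to however many other variables are screened, and the final set still depends on the data. An analysis plan could settle the cut, but to remove the problem it would have to override a selection rule that the article states outright.

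**Conclusion.** The point holds as a fault in a stated method. Covariates for the final PHQ-9 and HDRS-17 models, and for Aims 2 and 3, are selected by chance imbalance rather than prognostic value, from an open list with no cut. The final model is therefore unknown until allocation is seen. With six independent candidates, the chance that at least one qualifies ranges from 26% to 74% according to a threshold that the article does not give.

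The consequence is an unfixed primary analysis, not a demonstrated loss of power or an inflated error rate. The type I figures assume six independent covariates and R² of 0.10 to 0.30. The 0.035 to 0.039 further requires choice of the most favourable model. The forgone precision, about 1 to 10 points at 0.5 SD and 0.5 to 2 points at the planned effect, rests on the same assumed R² and does not apply to the condition-by-time test with main-effect covariates and complete data.

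**What to change.** Replace the selection sentence with a fixed covariate list, justified by prognostic value, used whatever the observed imbalance and set before anyone sees allocation. Age, sex and MDD treatment at baseline are reasonable examples: the first two are already named and the third is already collected. State for each whether it enters as a main effect or is crossed with time. Only the latter can bring a precision gain to the interaction when data are complete.

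State how baseline severity is handled, in one way only. Either keep it as the month-0 response, as now, or make it a covariate in a model of the 4- and 8-month scores alone. Adding the baseline score as a covariate while month 0 remains a response would use it twice.

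Move adjustment for imbalanced variables to a labelled sensitivity analysis, and carry the same list into Aims 2 and 3.

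The cost is a change of analysis wording and a few degrees of freedom. Three single-parameter covariates take 3, or 3 × 3 = 9 if each is crossed with the three time points, against 122 evaluable participants. Moving baseline to the covariate side would change the model, not just its wording. The article reports 18 of 146 enrolled in February 2024, so at that stage the change could be made well before outcomes were known.

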**Methods:**

This study involves a parallel-group, assessor-blinded RCT that examines the effect of a 4-month home-based exercise training intervention on depression severity in a sample of persons with MS who have MDD based on the MINI International Neuropsychiatric Interview. The primary outcomes of depression severity are the Patient Health Questionnaire-9 and Hamilton Depression Rating Scale. Participants (*N* = 146) will be recruited from within 200 miles of the University of Illinois at Chicago and randomized (1:1) into either a home-based exercise training condition or control condition with concealed allocation. The exercise training and social-contact, attention control (i.e., stretching) conditions will be delivered remotely over a 4-month period and supported through eight, 1:1 Zoom-based behavioral coaching sessions guided by social-cognitive theory and conducted by persons who are uninvolved in screening, recruitment, random assignment, and outcome assessment. We will collect outcome data at 0, 4 and 8 months using treatment-blinded assessors, and data analyses will involve intent-to-treat principles.

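### The Aim 1 mixed model leaves the arms' baseline means free although randomisation follows baseline, so its valid 4-month contrast is less precise than one that uses the baseline score

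*Protocol article*

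**What the plan says.** The section Data analysis – aim 1 gives the model: "The linear mixed model will include condition and time as fixed effects, and subject nested within condition as a random effect", fitted by REML. That sentence does not list the interaction, but a later one does: "The hypothesized interaction term will be decomposed with follow-up tests". The form of those follow-up tests is not given.

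Baseline is a level of time and not a covariate. The Methods paragraph of the abstract says "We will collect outcome data at 0, 4 and 8 months using treatment-blinded assessors". The power analysis is for a condition by "Time (2 levels of within-subjects factor: 0 and 4 months) interaction on the primary outcomes of depression severity". The Aim 1 hypothesis concerns "reductions from baseline in depression severity that (b) are sustained over 4-months of follow-up compared with those in the control condition".

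The Random assignment and Procedure sections both place randomisation after baseline data collection.

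On covariates, the Data analyses overview says "The confounders may include MS duration, BMI, age, sex, disease-modifying therapy, and relapse rate", followed by "We will include any of those variables and others that differ between conditions as covariates in the following analyses". Baseline PHQ-9 and baseline HDRS are not among the named variables.

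Aims 2 and 3 reuse the Aim 1 modelling approach.

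**The concern.** A condition main effect plus a condition-by-time interaction gives each arm its own baseline mean. Because allocation happens after baseline is measured, the true baseline difference is zero, and the model spends information estimating it. The 0-to-4-month contrast then subtracts the whole observed baseline difference, where an efficient analysis would subtract only the part that the baseline-to-follow-up correlation justifies.

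The covariate rule does not secure baseline adjustment. A baseline depression score would enter only if it happened to differ between the arms, and not because it predicts the outcome.

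What is at stake is precision on both primary outcomes and, through the shared approach, on the Aim 2 and Aim 3 outcomes. It matters most if the true effect is smaller than planned. The Discussion itself notes that the planning effect comes from samples not screened for MDD and may not represent this population.

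**Working it through.** **Inputs.** From Power analysis and sample size: f = 0.18, two-tailed alpha 0.025, power 95%, N = 122 (61 per arm), two time levels, and ICC 0.50 ("assumptions of reliability for the within-subjects factor"), read as the correlation rho between baseline and follow-up. From the Discussion: ½ SD, given as an example of a meaningful difference. The article gives no SDs at any visit. Equal SDs are therefore assumed first and then varied.

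**1. Reproduce the stated sample size.** For the repeated-measures within-between interaction with m = 2 levels, the noncentrality is f² × N × m / (1 − rho). At N = 122 this is 0.0324 × 122 × 2 / 0.50 = 15.81 on (1, 120) degrees of freedom, and power is 95.5%. The smallest even N reaching 95% is 120 (95.2%). The stated 122 is confirmed.

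**2. Translate f.** In this 2 × 2 interaction f is one quarter of the difference in change in SD units, so f = 0.18 means 4 × 0.18 = 0.72 SD. Check: 0.72² × 122 / (4 × 1.00) = 15.81, the same noncentrality.

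**3. What the planned contrast estimates.** In 400 simulated complete data sets (61 per arm, three visits, random-intercept REML fit), the 4-month interaction estimate equalled the difference in mean change to within 5 × 10⁻¹⁵. With dropout the equality is approximate.

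**4. Variance per participant, in units of the follow-up variance, equal SDs.**
- Change score: 2(1 − rho) = 2 × 0.50 = 1.00.
- Baseline-adjusted, or common baseline mean: 1 − rho² = 1 − 0.25 = 0.75.
- Ratio 0.75, a 25% reduction. 122 / 0.75 is about 163, so 122 participants would carry the information of about 163.

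Exact generalised least squares with three visits and 61 per arm gives 0.03279 against 0.02459 for the 4-month effect, again a ratio of 0.75. If the follow-up test were the plain arm difference at 4 months, its variance would also be 1.00, so the comparison does not depend on which of the two was meant.

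**5. Power at N = 122, alpha 0.025, rho = 0.50, equal SDs.**

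| True difference | Planned contrast | Using baseline |
|---|---|---|
| 0.72 SD (design effect) | 95.5% | 98.9% |
| 0.50 SD | 69% | 82% |

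**6. Sensitivity to rho, equal SDs.** The saving is (1 − rho)/2. At rho = 0.4 it is 30%, and power at ½ SD goes from 60% to 77%. At rho = 0.7 it is 15%, and power goes from 90% to 94%.

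**7. Sensitivity to the SD ratio, rho = 0.50.** If the baseline SD is k times the follow-up SD, the change-score variance is 1 + k² − 2 × 0.50 × k = 1 + k² − k, while the adjusted variance stays at 0.75. Power is for a difference of ½ follow-up SD.

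| k | Change variance | Saving | Planned power | Power using baseline |
|---|---|---|---|---|
| 1.0 | 1.00 | 25% | 69% | 82% |
| 0.9 | 0.91 | 18% | 73% | 82% |
| 0.8 | 0.84 | 11% | 77% | 82% |
| 0.7 | 0.79 | 5% | 80% | 82% |

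**The case against.** The strongest reply is that nothing here is wrong. The trial was sized on a condition-by-time interaction and tests that same interaction. The test is unbiased under randomisation, holds its type I error, and has its stated power at the effect it was planned for. At that effect the gain is only about 3 points. All of this stands.

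The 25% also assumes equal SDs. Table 1 selects participants on depression (a screening score and interview-confirmed MDD), which could narrow the baseline spread and shrink the saving. This stands too, and is why the range is shown.

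The covariate list is open-ended, so baseline severity is not excluded. That is true, but entry still depends on an observed imbalance.

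A reader might go further than the documents allow in three ways:
- **That the trial is underpowered at its own threshold.** The ½ SD is an example within a rule for moving to Phase III, not the alternative used for sizing. A mismatch between 0.72 and 0.50 SD is a sample-size question, not a fault of this model.
- **That the change closes most of the shortfall at ½ SD.** From 69% to the protocol's 95% is 26 points, and the change recovers 82 − 69 = 13, about half.
- **That regression to the mean biases the result.** In randomised arms it is equal in expectation. It acts only through chance baseline imbalance, and that is the same precision loss already counted.

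Finally, a condensed article may leave the exact contrasts to a fuller plan. But the model it does state is the less efficient one, so this is not a complaint about missing detail.

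**Conclusion.** The point holds as one of efficiency. The Aim 1 model as written frees a baseline difference that the design fixes at zero, and it does not commit to using the baseline score in any other way. With rho = 0.50, the cost is up to 25% of the variance of the 4-month effect when SDs are equal, falling to about 5% when the baseline SD is 0.7 of the follow-up SD. In power with equal SDs, it is worth about 3 points at the planned 0.72 SD and about 13 at ½ SD. These figures assume that the ICC is the baseline-to-follow-up correlation, and that data are complete on 122 participants.

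The documents do not support calling the planned analysis biased or invalid, or its 95% power misstated. This is a worthwhile improvement at almost no cost, not a correction of an error.

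**What to change.** Keep the 0-, 4- and 8-month scores as outcomes, but give both arms one common baseline mean. The fixed effects become time plus condition-by-follow-up-visit terms, with no condition effect at baseline. An unstructured covariance is preferable to the random intercept alone, because it does not force equal variances across visits. State the 4- and 8-month condition terms as the contrasts, and prespecify the same form for Aims 1 to 3.

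This keeps every randomised participant with a baseline score in the model, in line with the stated intent-to-treat definition. It needs no new data. The article reports 18 people enrolled at its status date and a data lock before analysis, so there was still room to prespecify it then.

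An alternative is to model only the 4- and 8-month scores, with baseline score and its interaction with visit as covariates. Its drawback is that anyone with no follow-up score contributes nothing, which sits badly with including all participants regardless of dropout.
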